### Statistical analysis

Primary analyses will be on an intention to treat basis, with supplementary ‘per protocol’ analyses (at least 75% of staff enrolled in the study completing at least 75% of training sessions). To account for the within-facility clustering and repeated assessments of staff and residents, hypothesized main effects for outcomes will be tested using a multilevel linear (or generalized linear, where appropriate) regression modelling. For each outcome, a separate three-level regression model will be specified, with repeated measurements as level 1, individuals as level 2, and facility as level 3. The regression models will include Condition allocation, assessment time point, and Condition by time interaction as predictors. Facilities and individuals will be modelled as random effects with remaining variables modelled as fixed effects. Missing data will be handled with conditional maximum likelihood estimation. The impact of possible non-random attrition will be explored with simulation analyses.

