### Hypotheses and expected outcomes

It is hypothesized that, relative to care as usual, the RCC Program will improve residents’ QoL (Primary Outcome Measure – QoL at 6-months follow-up); their perceptions of their level of choice and control and the working relationship with staff (Secondary Outcome Measures). It is also hypothesized that the RCC Program will lead to organizational change; improve staff perceptions of their use of transformational leadership, job satisfactions, working relationship with residents, experience of CDC; reduce their job stress and intention to quit (Secondary Outcome Measures). Supplementing the RCC Program with extra support to assist staff to address barriers to CDC implementation and so implement change is hypothesized to lead to greater benefits than the same program without this support. These changes are predicted to occur, relative to baseline at 3-months, 6-months, and 12-months follow-up.

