**Fig. 1 Fig1:**
[figure not shown]
Flow chart of staff recruitment, baseline, roll out of the program, post-intervention and follow-up

A 0.5 FTE study champion appointment will be made by each organization. This study champion will be recruited from the commencement of the study, with a brief to work with staff and the research team to assist in the roll out of the strategies identified as a result of the training program. This study champion will assist in the recruitment of staff and residents for the study as well as assist staff to embed the strategies from the program into routine practice. The study champion will be an important link between the staff in the two intervention facilities and the research team implementing the protocol. In addition to the organizational support provided for Condition 1, the study champion will assist staff to overcome barriers to CDC implementation throughout the 15 months of the study period. The overall study will run from January 2018 through to December 2020. The first round of staff and resident recruitment and data collection commenced in May 2018 and it is anticipated the final round of data collection will be completed by July 2020. The roll-out of the training program will run from June 2018 to July 2019. The second half of 2020 will be dedicated to data analysis and interpretation, and writing of publications.

Informed by the results of our earlier NHMRC-funded RCT (APP1042156) our study is designed to detect a moderately small difference *d* ≥ 0.35 between the RCC plus organizational support and control Condition in QoL of residents at 6-months follow up (primary outcome) and in staff outcomes post-intervention (secondary outcomes). We selected 6-months follow up as our primary endpoint for residents’ QoL because we expect a gradual and continuing change in this outcome as a result of changing practice. Allowing for 80% power, 5% Type I error rate (2-tailed), intra-class correlation of 0.02 for the within-facility clustering, and 25% (residents) and 33% (staff) attrition over time, we will need to randomize at least 744 residents (248 per Condition) and 834 staff (278 per Condition). Based on our previous work in the residential aged care setting, we expect an average recruitment of 20 residents and 22 staff per site. Hence, 39 aged care facilities will need to be enrolled into the study (13 for each arm of the RCT). Data analysis is discussed later in the Methods/Design section.

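### The analysis section names main effects as the test, but the primary, powered comparison is Condition 1 versus Condition 3 at 6 months; name that contrast and give the conditions a common baseline mean

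*Protocol article*

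**What the plan says.** Three places in the protocol article bear on which test is primary.

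- **Hypotheses and expected outcomes** makes resident quality of life at 6 months the primary outcome. The hypothesis is worded as the RCC Program against care as usual, although two arms receive that program. It adds that the extra organizational support "is hypothesized to lead to greater benefits than the same program without this support", and it predicts changes from baseline at 3, 6 and 12 months.
- **Study design**, in the sample-size paragraph, is narrower. The study is "designed to detect a moderately small difference" of d = 0.35 or more "between the RCC plus organizational support and control Condition in QoL of residents at 6-months follow up (primary outcome"). The inputs are "Allowing for 80% power, 5% Type I error rate (2-tailed), intra-class correlation of 0.02 for the within-facility clustering". Loss to follow-up is put at a quarter of residents and a third of staff. The stated requirement is "at least 744 residents (248 per Condition) and 834 staff (278 per Condition").
- **Statistical analysis** says that "hypothesized main effects for outcomes will be tested using a multilevel linear" (or generalized linear) model with three levels: visits, individuals and facilities. The fixed effects are Condition, time point and Condition by time. The section names neither a visit nor a pair of conditions for the primary test.

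**The concern.** In a model that contains a Condition-by-time interaction, a Condition main effect has a definite meaning, and it is not the 6-month difference. Taken at its word, the section describes a test of something other than the endpoint on which the sample size rests. The sample-size paragraph expects quality of life to change gradually, and averaging in the early visits dilutes that pattern.

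Two things are at stake. The first is power, if the statement is followed literally. The second is clarity about what was prespecified: the visit-averaged effect, the interaction, a comparison of either or both trained arms with control, and the 6-month contrast could each be presented later as the planned primary test.

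**Working it through.** **1. The plan's own figure.** Per arm, n = 2(1.960 + 0.842)²/0.35² = 128.1, so 129 (130 by t-test). With 22 per facility the design effect is 1 + 21 × 0.02 = 1.42, and 129 × 1.42/0.75 = 244.2, so 245 (247 from 130). With 20 per facility it is 1.38, giving 238-240. The stated figure is 248. Conversely, 248 × 0.75 = 186 evaluable per arm. This is an effective 186/1.42 = 131.0 or 186/1.38 = 134.8, with power 80.9% or 81.9%. The sample size is therefore adequate for one pairwise comparison at the full two-sided 5%.

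**2. What the main effect is.** Write the mean for condition g at visit t as μ + α_g + τ_t + γ_gt.
- With baseline as the reference visit, α₁ − α₃ is the baseline difference, which has expectation 0 under randomization.
- With effect coding, α₁ − α₃ is the mean of the four visit-specific differences, baseline included.
- The 6-month difference is (α₁ − α₃) + (γ₁,₆ − γ₃,₆). It can be estimated from the stated model but is not a main effect.

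**3. Power of the two tests.** From the document: ICC 0.02, 13 facilities per arm, and 20 × 0.75 = 15 residents analysed per facility. Assumed: SD 1, cluster autocorrelation 0.8, the same within-person correlation r (0.4 to 0.7) between all visits, Condition 1 effects of 0, 0.175, 0.35 and 0.35 SD, and t on 24 df.
- Facility-mean variance at one visit: V = 0.02 + 0.98/15 = 0.0853.
- Covariance between visits: C = 0.02 × 0.8 + 0.98r/15, which is 0.0421 at r = 0.4 and 0.0617 at r = 0.7.
- Unadjusted 6-month contrast: SE = √(2 × 0.0853/13) = 0.1146; 0.35/0.1146 = 3.05; power 83%. This is slightly above step 1 because it uses 195 evaluable per arm and a design effect at 15 per facility.
- Visit-averaged main effect: (0 + 0.175 + 0.35 + 0.35)/4 = 0.219 SD, with variance (V + 3C)/4.

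| r | SE of averaged effect | Power, 12-month effect 0.35 | Power, 12-month effect 0.525 |
|---|---|---|---|
| 0.4 | 0.0902 | 64% | 80% |
| 0.7 | 0.1020 | 54% | 70% |

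The last column uses an average of 1.05/4 = 0.2625 SD. A simpler check with 186 evaluable, design effect 1.42 and r = 0.5-0.7 gives 52-61% for the plateau course and 68-77% for the growing one.

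**4. Use of baseline.** Let ρ = C/V: 0.494 at r = 0.4 and 0.723 at r = 0.7. Difference-in-change, as the free-baseline model gives it, has variance proportional to 2V(1 − ρ). With a common baseline mean, or baseline as covariate, it is V(1 − ρ²). The ratio is (1 + ρ)/2.

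| r | Ratio | Variance cut | Power, difference-in-change | Power, baseline-adjusted (23 df) |
|---|---|---|---|---|
| 0.4 | 0.747 | 25% | 83% | 92% |
| 0.7 | 0.862 | 14% | 98% | 99% |

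**The case against.** The best defence is that main effects is loose wording for the principal hypothesized effects. The model includes Condition by time, the hypotheses speak of change from baseline at named visits, and the sample-size paragraph fixes both the visit and the pair of conditions. Read together, these point to the 6-month contrast, and few analysts would test the baseline difference as a treatment effect. This stands to the extent that the model can deliver the right test. It does not make the sentence right: the one place that says what will be tested names something else, and the hypotheses do not settle which trained arm is meant.

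The power loss depends on the assumed time course. If the effect goes on growing to 12 months, the averaged test loses much less, as the table shows. Difference-in-change is also a valid, standard analysis that meets the planned 80% on these inputs, so the baseline point concerns efficiency and not an error.

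A reader might further infer that several comparisons share an unprotected 5%, with familywise error of 9.1% for two comparisons against control or 12.2% for all three pairs. The document does not support that. It gives 5% only for the one powered comparison and never says that every contrast is tested at that level. A testing order may stand in an analysis plan not shown. A reader might also conclude that Condition 1 versus 2 has only 31% power. That figure assumes that Condition 2 achieves half of 0.35 and ignores baseline adjustment; with adjustment it is about 39-56%. The document gives no expected effect for Condition 2.

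**Conclusion.** The stated test does not match the stated primary endpoint and powered comparison. Taken literally, it replaces a 6-month contrast with about 83% power by a visit average with about 54-64%, or 70-80% if the effect keeps growing, or by a baseline difference with expectation 0. These figures rest on the assumed effect courses, cluster autocorrelation 0.8 and within-person correlation 0.4-0.7, none of which the document gives.

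The defect lies in the naming of the test. The Condition-by-time term makes the right contrast estimable, so it would be wrong to infer that the model cannot test the primary hypothesis. The stated sample size is not wrong, and the absence of a multiplicity rule from the article is not itself an error. Separately, the free baseline mean per condition forgoes a variance reduction of about 14-25% against difference-in-change, which baseline data already planned for collection would provide.

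**What to change.** 1. In Statistical analysis, replace main effects by one primary test: the Condition 1 versus Condition 3 difference in resident quality of life at 6 months, two-sided 5%, from the same multilevel model.
2. Fit a common baseline mean for all conditions (constrained longitudinal model), or enter baseline quality of life as a covariate.
3. State that Condition 2 versus 3 and Condition 1 versus 2 are secondary, or are tested in that fixed order after the primary test, because the sample size covers one comparison at the full 5%. Align the wording of the hypotheses with this.
4. Say that Condition 1 versus 2 was not the basis of the sample size and will be read from its confidence interval.

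The cost is a few sentences and a small change in model specification. No extra residents or assessments are needed: at 248 per Condition the named contrast has about 81-82% power before any gain from baseline. If the fixed order is chosen, a later comparison cannot be claimed once an earlier one fails.

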### Evaluation of the training program

#### Evaluation measures for aged care residents

The following measures will be completed by the residents at baseline and 3 months, 6 months, and 12 months follow-up. A research assistant who is blind to the condition will individually sit with each resident and work through the measures listed below.

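### The outcome model gives each arm its own baseline mean and does not adjust for baseline, which costs precision on the primary 6-month comparison

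*Protocol article*

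**What the plan says.** The Statistical analysis section sets out one three-level model per outcome, "with repeated measurements as level 1, individuals as level 2, and facility as level 3". On the fixed part it says: "The regression models will include Condition allocation, assessment time point, and Condition by time interaction as predictors". On the random part: "Facilities and individuals will be modelled as random effects with remaining variables modelled as fixed effects". It lists no baseline covariate, no constraint on the baseline means and no facility-by-time term, and it does not identify the coefficient or contrast that is the primary treatment effect.

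Baseline is one of the repeated assessments: "The following measures will be completed by the residents at baseline and 3 months, 6 months, and 12 months follow-up".

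Two other places bear on the contrast, and they point in different directions. The Hypotheses section makes quality of life at 6 months the primary outcome, but words the expected effects as change: "These changes are predicted to occur, relative to baseline at 3-months, 6-months, and 12-months follow-up". The sample-size paragraph of the Study design section instead targets a difference "between the RCC plus organizational support and control Condition in QoL of residents at 6-months follow up (primary outcome"), that is, a between-arm difference at one visit.

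**The concern.** If baseline is a row of the outcome and Condition has a main effect, the model estimates three separate baseline means. The 6-month Condition by time coefficient is then the between-arm difference in change from baseline, which subtracts the whole observed baseline difference. If the 6-month difference is instead taken from the same model, separate arm means at every visit imply that, with complete data, baseline contributes nothing and none of the baseline difference is subtracted. The efficient weight lies between these two. Including baseline as a free outcome is therefore not baseline adjustment.

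At stake is precision on the primary outcome and on those secondary outcomes that have a pre-intervention measurement. The baseline data are already being collected.

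**Working it through.** **The plan's own figure.** The inputs are d = 0.35 and "Allowing for 80% power, 5% Type I error rate (2-tailed), intra-class correlation of 0.02 for the within-facility clustering", with "25% (residents) and 33% (staff) attrition over time".

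- Two-mean formula: 2 × (1.960 + 0.842)² / 0.35² = 128.1, so 129 per arm.
- Design effect with 23 per facility: 1 + 22 × 0.02 = 1.44. Then 129 × 1.44 = 185.8, so 186 evaluable per arm.
- Residents: 186 / 0.75 = 248. Staff: 186 / 0.67 = 277.6, so 278.

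Both stated figures reproduce. With 22 per facility the results are 246 and 275. With the 20 residents per site that the article expects, the result is 239. No baseline correlation enters, so the trial is sized for an unadjusted difference at 6 months.

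**Set-up for the variance comparison.** Total variance is 1, ICC is 0.02, and there are k = 13 facilities per arm. Evaluable residents per facility are m = 248 × 0.75 / 13 = 14.3, taken as 14. The random effects are the plan's: constant facility and individual intercepts. The within-resident correlation r (between visits, within facility) is an assumption, because the article gives none. Blocking by organization is ignored.

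- Variance of a facility mean at one visit: V = 0.02 + 0.98/14 = 0.090.
- Covariance of the baseline and 6-month facility means: C = 0.02 + 0.07r.
- Change contrast: (4/k)(V − C).
- Unadjusted 6-month difference: (2/k)V.
- Baseline-adjusted difference: (2/k)(V − C²/V).
- Saving against the change contrast: (V − C)/(2V) = 0.389(1 − r).
- Saving against the unadjusted difference: (C/V)².
- Efficient weight on the baseline difference: C/V. The change contrast uses 1 and the unadjusted difference uses 0.

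| r (assumed) | C | C/V | Change | Unadjusted | Adjusted | Saving vs change | Saving vs unadjusted |
|---|---|---|---|---|---|---|---|
| 0.5 | 0.055 | 0.61 | 0.01077 | 0.01385 | 0.00868 | 19.4% | 37.3% |
| 0.6 | 0.062 | 0.69 | 0.00862 | 0.01385 | 0.00728 | 15.6% | 47.5% |
| 0.7 | 0.069 | 0.77 | 0.00646 | 0.01385 | 0.00571 | 11.7% | 58.8% |

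**Range.** From 0.389(1 − r), the saving against the change contrast is 25.3% at r = 0.35 and 9.7% at r = 0.75, hence roughly 10–25%.

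**Sensitivity.**

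- *Facility effects that vary over time.* With an assumed facility autocorrelation of 0.8, C becomes 0.016 + 0.07r. The savings against the change contrast are 21.7%, 17.8% and 13.9% at r = 0.5, 0.6 and 0.7. The plan specifies no such term.
- *Residents with baseline only.* In an exact generalised least squares calculation with 20 residents per facility and constant facility effects, total within-resident correlations of 0.4 to 0.6 give savings of 21.7% to 14.5% with complete data. If 25% are lost before the first follow-up, these become 17.7% to 11.5%.

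**Power at d = 0.35** (normal approximation, Φ(0.35/√variance − 1.96), variances from the table). The unadjusted difference has about 84%. The change contrast has 92%, 97% and 99% at r = 0.5, 0.6 and 0.7. The adjusted estimate has 96%, 98% and above 99%.

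**The case against.** The strongest reply is that this is a preference between valid methods. The planned model is a standard repeated-measures specification, it is unbiased under randomisation, and it fits the change wording of the Hypotheses section. On the figures above it also meets the planned 80% power. All of that stands. A reader might infer that the analysis is wrong or the trial underpowered; the documents support neither.

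A reader might also infer that the treatment effect is definitely a change-score difference. The article names no contrast and sizes the trial on the 6-month difference, so that is only one of two readings. The point survives because adjustment is more precise than either.

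A fixed saving obtained at no cost is not supported either. The size depends on an unreported correlation. The shared baseline mean follows from randomisation only if enrolment is independent of allocation. The article does not say that recruitment precedes allocation. Facilities identify eligible residents, and the study champion both helps recruit and links the intervention facilities to the research team. If enrolment were selective, forcing equal baseline means would attribute part of a real baseline difference to treatment, so leaving baseline free has a rationale. Comparing the two fits cannot prove that enrolment was unselected.

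The argument from chance imbalance with 13 facilities per arm is also weaker than it looks. Each organization supplies three facilities, which are then allocated to the conditions; if one goes to each condition, imbalance due to organization is limited.

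Finally, an analysis plan that is not shown could add baseline adjustment. That is possible, but a shared baseline mean would mean dropping a predictor that the article lists, so the published specification merits comment.

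**Conclusion.** The point holds as a cheap gain in efficiency; it does not identify an error. As published, the model does not adjust for baseline and leaves the primary contrast unnamed. A baseline-adjusted 6-month difference has lower variance than either contrast the model offers: by roughly 10–25% against the change contrast for within-resident correlations of about 0.35 to 0.75, and by more against the unadjusted difference at correlations of 0.5 to 0.7.

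These sizes assume the stated ICC of 0.02, about 14 evaluable residents per facility, constant facility and individual effects, and correlations that are not in the documents. The gain does not extend to every repeated outcome. Readiness for change is first measured after Session 3, so it has no pre-intervention value to adjust for or constrain.

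**What to change.** Name the between-arm difference in quality of life at 6 months as the primary contrast, and estimate it with baseline adjustment in one of two ways:

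- model the 3-, 6- and 12-month values with individual and facility-mean baseline as covariates; or
- keep baseline in the outcome, drop the Condition main effect, and retain time and Condition by post-baseline time, so that all arms share one baseline mean.

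The two are similar but not identical, so the text should commit to one. Report the present unconstrained model as a sensitivity analysis. Restrict the change to outcomes with a pre-intervention measurement, which excludes readiness for change.

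The cost is a sentence or two in the Statistical analysis section and no new data. The covariate version needs a rule for participants with no baseline value. The shared-mean version needs a statement of whether residents and staff were enrolled before allocation was known; if they were not, its assumption is open to doubt.

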## Methods/design

### Study design

A cluster randomized controlled trial design will be employed in this study, with 39 facilities randomly allocated to one of three conditions (13 facilities in each). Each of the 13 aged care organizations will provide three separate facilities to take part in the study, which will then be randomly allocated to one of the three conditions. Allocations of facilities will be completed by the biostatistician not involved in data collection using random numbers generated at random.org.

The first condition will involve the delivery of the five-session RCC Program plus additional organizational support. This organizational support is designed to assist staff to implement the CDC model of care within their facility. It will be provided one day a week for four weeks following Session 3 and a further one day a week for 12 weeks following Session 5. This training is above and beyond what is provided within each session of the training program, and is designed to assist staff in applying their learnings from the program (in line with the facility’s CDC implementation plan) and assist the staff to work through challenges as they arise. Sessions 4 and 5 will occur immediately after a four-week gap (see Fig. 1). The second condition will be a second intervention group, where staff will be provided with the RCC Program without the additional organizational support. The third condition will be a ‘care as usual’ control group. Staff will be provided with paid release time to attend the program. Data from the residents will be collected by a research assistant who is blind to the condition to which the facility is allocated.

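### The facility effect is constant over time, so the change-from-baseline contrast does not protect the 5% type I error if facilities drift apart

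*Protocol article*

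**What the plan says.** The Statistical analysis section sets out the levels of the model as follows: "a separate three-level regression model will be specified, with repeated measurements as level 1, individuals as level 2, and facility as level 3". On the predictors it says "The regression models will include Condition allocation, assessment time point, and Condition by time interaction as predictors". It then divides the terms into random and fixed: "Facilities and individuals will be modelled as random effects with remaining variables modelled as fixed effects". The section gives accounting for within-facility clustering and repeated assessment as the purpose of this model.

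Under Hypotheses and expected outcomes, the primary outcome is resident quality of life at 6 months, and the expected effects are described as changes: "These changes are predicted to occur, relative to baseline at 3-months, 6-months, and 12-months follow-up". The sample-size paragraph under Study design instead speaks of a difference of "0.35 between the RCC plus organizational support and control Condition in QoL of residents at 6-months follow up", with one ICC of 0.02 and no correlation of facility effects between time points. Facilities are the randomised units, 13 per condition.

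**The concern.** The word intercept does not appear, but time is one of the remaining variables and so belongs to the fixed part. As written, no facility slope and no facility-by-visit term is in the model. Each facility shifts its residents' scores by the same amount at baseline and at every follow-up.

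That shift disappears when baseline is subtracted. The Condition-by-time contrast is then judged against within-person residual variation alone, and between-facility variation drops out of its error term although facilities were randomised. This is harmless only if facilities do not move relative to one another. The program acts through leadership, climate and practice in each facility, and ordinary local change also occurs in control facilities, so some divergence is plausible. If it occurs, confidence intervals for change are too narrow and false positives exceed 5%. The same model form is used for every resident and staff outcome.

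**Working it through.** **The article's own figure.** For d = 0.35, 80% power and two-sided 5%, a two-sample comparison needs 129 per arm. A design effect of 1 + 22 × 0.02 = 1.44 gives 129 × 1.44 = 186 analysed per arm. Then 186/0.75 = 248 residents and 186/0.67 = 278 staff per condition, as stated. (The exact match for residents uses 22 per site, not the stated 20. This does not affect the present point.) The calculation applies the full ICC at a single time point.

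**Inputs from the article.** 13 facilities per arm; ICC 0.02; 20 residents per facility less 25% attrition, so m = 15. Staff numbers are similar (22 × 0.67 = 14.7).

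**Assumptions not in the article.** Total variance is 1. The facility variance of 0.02 splits into a stable part 0.02 × c and a facility-by-visit part s²_ft = 0.02 × (1 − c), where c is the correlation of a facility's effect between visits. The within-person correlation r, after removing the facility part, is 0.5 to 0.7, so the residual variance is s²_e = 0.98 × (1 − r). Data are balanced, with four visits.

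**Formulas for the arm difference in change, 6 months minus baseline.**
- True variance: 4 × [s²_e/(13m) + s²_ft/13]
- Variance reported by the stated model: about 4 × (s²_e + s²_ft)/(13m), because s²_ft is absorbed into the residual and divided by 15 residents as if independent between them
- Actual type I error: 2 × [1 − Φ(1.96/R)], where R = true SE / model SE

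**Worked example, c = 0.5 and r = 0.5.** s²_ft = 0.01 and s²_e = 0.49. Model SE = √(4 × 0.50/195) = 0.1013. True SE = √[4 × (0.49/195 + 0.01/13)] = 0.1146. R = 1.131, and the actual error is 8.3%.

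| Facility correlation c | R (r = 0.5 to 0.7) | Actual type I error |
|---|---|---|
| 1.0 | 1.00 | 5% |
| 0.9 | 1.03 to 1.05 | 5.7 to 6.1% |
| 0.8 | 1.06 to 1.09 | 6.3 to 7.2% |
| 0.5 | 1.13 to 1.21 | 8.3 to 10.5% |
| 0 | 1.25 to 1.38 | 11.5 to 15.4% |

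Simulation (5,000 trials per setting) agrees: at c = 0.5, for example, it gives 8.1% and 10.2%. A test that uses the facility-by-time mean square as its error term held 4.5 to 5.7% in the same runs.

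**The other candidate contrast.** For the plain between-arm difference at 6 months the facility effect does not cancel. Simulation with the same inputs, the random-intercept model and 36 degrees of freedom (also an assumption) gave 4.7 to 4.9% at c = 0.9, 5.0 to 5.2% at 0.8 and at 0.5, and 5.9 to 6.0% at 0. A closed-form check with a normal reference gives about 6% at 0.5 and 7% at 0.

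**Power after the change.** For d = 0.35 on the change contrast with m = 15, power is 0.92 to 0.99 at c = 0.9 and 0.79 to 0.89 at c = 0.

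**The case against.** The strongest objection concerns the contrast. The primary outcome is named as quality of life at 6 months, the power statement describes a between-arm difference at that visit, and the Statistical analysis section speaks of testing hypothesised main effects. The stated model can deliver that between-arm difference, and on that reading there is almost no inflation. This stands. The relative-to-baseline sentence and the Condition-by-time term support the change reading equally well, and the article does not say which contrast is the primary test.

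Second, inflation needs facility-by-time variance, and the article gives no value for it. This also stands: the result is a range, and its top needs a facility's baseline level to say nothing about its level six months later, which is extreme for the same residents in the same homes.

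Third, an article condenses, and covariance details and degrees of freedom commonly go to the analysis plan. This holds for the degrees of freedom. It holds less for the random part, because the article positively assigns every term other than facility and individual to the fixed part.

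A reader might also infer more from "Missing data will be handled with conditional maximum likelihood estimation": literally, conditioning would remove the facility-level Condition term. In context the sentence is about missing data and sits beside explicit random effects, so it reads as loose wording for likelihood estimation on available data. It adds nothing to this point.

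**Conclusion.** The point holds conditionally. As written, the model leaves facility-level change out of the error term for change from baseline, so the 5% level for that contrast is not protected. Under the assumptions above, the actual level is about 6 to 7% for facility correlations of 0.8 to 0.9, 8 to 10.5% at 0.5, and 11 to 16% (closed form and simulation together) only at zero.

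A reader might infer that the trial's standard errors are certainly too small, or that the primary test fails its stated 5% level. The article supports neither: the facility-by-time variance is unknown, and the 6-month between-arm difference, an equally admissible primary contrast, stays near 5 to 6%. Nor does the point undermine the sample size, which uses the full ICC at one time point. This is a cheap and worthwhile improvement, not a must-fix.

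**What to change.** Add a random facility-by-time effect (facility × visit, nested in facility) to each model. Use a small-sample degrees-of-freedom correction suited to 13 facilities per arm. State whether the primary test is the arm difference in change from baseline or the between-arm difference at 6 months.

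The cost is a sentence or two, one more variance component and slightly wider intervals. The component may be estimated at zero: at facility correlations of 0.8 to 0.9 this would occur in 11 to 36% of simulated trials, and the fit then falls back to the stated model. The checks above used a facility-by-time mean square and did not fit the full mixed model, so its error rate should be confirmed by simulation before the plan is finalised.
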